#### Traditional intervention

2.6.2.

The CG involves the activities usually offered at the Day Care Center, such as cognitive stimulation (reality orientation therapy, cognitive training) and occupational activities (painting workshops, cooking workshops, garden therapy, music therapy, etc.).

#### Equipment

2.6.3.

Paro is a seal-shaped robot designed to have a calming effect and elicit emotional responses in patients in hospitals, nursing homes, and retirement homes. The robotic pup is 55 centimeters long, weighs less than three kilograms and is capable of moving its eyes, head, front and lower flippers. Paro also has many sensors that make him photosensitive and able to respond to tactile stimulation, even on his whiskers. Thanks to the presence of the three microphones, it is able to recognize the patient’s voice and is even capable of learning new information such as the subject’s name and behavioral characteristics, all thanks to advanced artificial intelligence. The robot also has the ability to “play” with the patient, thanks to autonomous behaviors that mimic those of a real pet.

### Outcomes

2.7.

All outcome measures follow a standardized operating procedure. Table 1 shows the primary outcome and the secondary outcomes.

**Table 1 tab1:** Outcomes and clinical assessments.

Outcome(s)	Clinical assessment
*Primary*: Quality of life (patient)	QoL-AD
*Secondary*: Cognitive status (patient)	ACE-R
*Secondary*: Anxiety (patient)	RAID
*Secondary*: Depression (patient)	CSDD
*Secondary*: Acceptance of technology (patient)	QUEST 2.0 semi-structured interview observation by the operator
*Secondary*: Behavioral symptomatology (patient)	NPI
*Secondary*: Acceptance of technology (operator)	TAM
*Secondary*: Quality of work	Semi-structured interview

QoL-AD, Quality of Life – Alzheimer’s Disease; ACE-R, Addenbrooke Cognitive Examination; RAID, Rating Anxiety In Dementia; CSDD, Cornell Scale for Depression in Dementia; QUEST 2.0, Quebec User Evaluation of Satisfaction; NPI, Neuropsychiatric Inventory; TAM, Technology Acceptance Model.

A summary of all data collected and when these are collected is provided ion Table 2.

**Table 2 tab2:** Schedule of assessment and outcome measures.

Scale	R	T0	T1	T2
Socio-demographics checklist	X			
Mini Mental State Examination (MMSE)	X			
Addenbrooke Cognitive Examination (ACE-R)		X	X	X
Hamilton Anxiety Rating Scale (HAM-A)		X	X	X
Cornell Scale for Depression in Dementia (CSDD)		X	X	X
Quebec User Evaluation of Satisfaction (QUEST 2.0)			X	
Semi-structured interview for patient technology acceptance			X	
Quality of Life – Alzheimer’s Disease (QoL-AD)		X	X	X
Neuropsychiatric Inventory (NPI)		X	X	X
Technology Acceptance Model (TAM)			X	
Semi-structured interview for technology acceptance and workload for operator			X	

R, Recruitment; T0 = Start of intervention; T1 = End of intervention (12 weeks from T0); T2 = Follow-up at 3 months (24 weeks from T0).

The scales used during the evaluations are described below.

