**Methods and analysis:**

For this study, 20 patients with dementia are recruited and divided into Experimental Group (EG) and Control Group (CG). Twenty-four session of intervention are conducted, divided into 2 sessions per week, for 12 weeks. The therapy sessions last 20 min. The Experimental Group will receive a social robotic intervention with Paro combined with usual care; the Control Group will receive only the traditional therapy, consisting of cognitive stimulation (reality orientation therapy, cognitive training) and occupational activities (painting workshops, cooking workshops, garden therapy, music therapy, etc.). Paro is a seal-shaped robot designed to have a calming effect and elicit emotional responses in patients in hospitals, nursing homes, and retirement homes. Assessment will be performed at the baseline, at the end of intervention and 3 months after the end of intervention. During these phases, several scales will be administered to the patients, such as Quality of Life—Alzheimer’s Disease, Addenbrooke’s Cognitive Examination, the Rating Anxiety In Dementia scale and the Cornell Scale for Depression in Dementia, Quebec User Evaluation of Satisfaction, Neuropsychiatric Inventory, the Technology Acceptance Model.

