### Trial design

2.1.

The study is designed as a pilot single blinded (outcome assessors) randomized controlled trial, with 3-month follow-up, in a group of 20 subjects with dementia, in order to evaluate the improvement in patient-perceived quality of life following the use of the Paro robot integrated with traditional intervention in the older people with dementia. The Experimental Group (EG) will receive a social robotic intervention with Paro combined with traditional one. The Control Group (CG), on the other hand, will receive only the usual care. Assessment will be performed at the baseline (T0), at the end of intervention (after 12 weeks -T1) and 3 months after the end of intervention (follow-up T2).

The primary aim is to evaluate the patient-perceived improvement in terms of quality of life through Quality of Life—Alzheimer’s Disease (QoL-AD), following the use of the Paro robot, integrated with usual care carried out within the IRCCS INRCA Alzheimer’s Day Center.

The Secondary aims are the evaluation of the improvement in cognitive status of the older person with dementia, in terms of orientation, attentional-executive, visuospatial functions, detected through the Addenbrooke’s Cognitive Examination (ACE-R); the assessment of mood improvement in terms of reduction of anxiety and depression, detected through the Rating Anxiety In Dementia (RAID) scale and the Cornell Scale for Depression in Dementia (CSDD); the assessment of the older person’s acceptance of the technology through Quebec User Evaluation of Satisfaction (QUEST 2.0), semi-structured interview and analysis of physiological activation during interaction, with the Noldus Face Reader system and direct observation by the operator; the analysis of behavioral symptomatology through Neuropsychiatric Inventory (NPI); the assessment of practitioner’s acceptance of technology through Technology Acceptance Model (TAM) and the assessment of job quality through semi-structured interview.

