#### Hamilton anxiety rating scale

2.7.3.

The HAM-A was one of the first rating scales developed to measure the severity of anxiety symptoms, and today it is still widely used in both clinical and research settings. The scale consists of 14 items, each defined by a set of symptoms, measures of both psychic anxiety (mental agitation and psychological distress) and somatic anxiety (anxiety-related physical complaints). Although the HAM-A remains widely used as an outcome measure in clinical trials, it has been criticized for its sometimes poor ability to distinguish anxiolytic effects from antidepressant effects and somatic anxiety effects from secondary somatic effects. The HAM-A does not provide any set of standardized questions. Despite this, the reported levels of reliability of the scale appear to be acceptable. Each item is scored on a scale from 0 (not present) to 4 (severe), with a total score range of 0–56, where <17 indicates mild, 18–24 mild to moderate, and 25–30 moderate to severe (31).

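### The anxiety outcome has two incompatible definitions: RAID where outcomes are declared, HAM-A where visits are scheduled and scales described

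*Protocol article*

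**What the plan says.** Three places in the protocol article tie anxiety to RAID:

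- The abstract (Methods and analysis) lists "the Rating Anxiety In Dementia scale and the Cornell Scale for Depression in Dementia" among the measures.
- Section 2.1 states the mood aim as a reduction in anxiety and depression, "detected through the Rating Anxiety In Dementia (RAID) scale and the Cornell Scale for Depression in Dementia (CSDD").
- Table 1 in section 2.7 pairs the secondary outcome of patient anxiety with RAID, and its footnote spells out "RAID, Rating Anxiety In Dementia".

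Two places tie anxiety to a different scale:

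- Table 2 in section 2.7 schedules the "Hamilton Anxiety Rating Scale (HAM-A") at T0, T1 and T2. The sentence before the table says: "A summary of all data collected and when these are collected is provided".
- Section 2.7.3 is devoted to HAM-A, with its items, scoring and a citation. The subsections are introduced with "The scales used during the evaluations are described below", and none of 2.7.1 to 2.7.8 covers RAID.

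**The concern.** An outcome is defined by its instrument as well as its construct. Here the construct (anxiety) is stable, but the instrument depends on which part of the article is read. Someone writing the analysis from section 2.1 and Table 1 would look for RAID scores. Someone preparing visit forms from Table 2 would provide HAM-A.

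Two things are at stake. First, as long as both names stand, either scale can later be presented as the planned one, so the choice could be made after results are known. Second, a comparison of change needs the same scale at T0. If the scale eventually reported was not given before the robot sessions began, its baseline cannot be recovered.

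**Working it through.** The point rests on no figure, so the check is a comparison of every place where an anxiety scale is named.

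| Place | RAID | HAM-A |
|---|---|---|
| Abstract, Methods and analysis | yes | no |
| Section 2.1, secondary aims | yes | no |
| Table 1 and footnote | yes | no |
| Table 2, schedule | no | yes (T0, T1, T2) |
| Sections 2.7.1 to 2.7.8 | no | yes (2.7.3) |

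The split is complete: three places name only RAID, two name only HAM-A, and none names both.

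**From declared outcomes to schedule.** The abstract names seven scales: QoL-AD, ACE-R, RAID, CSDD, QUEST 2.0, NPI and TAM. Six of the seven have a row in Table 2 and a subsection in 2.7. RAID is the only one with neither.

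**From schedule to declared outcomes.** Five scales in Table 2 are repeated at T0, T1 and T2: ACE-R, HAM-A, CSDD, QoL-AD and NPI. Four of them appear in Table 1 against an outcome. HAM-A is the only one that does not.

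So the mismatch is specific to anxiety and runs in both directions.

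**Size if Table 2 is taken literally.** RAID has 0 of 3 planned assessments. With 20 patients and no dropout, 20 × 3 = 60 anxiety assessments would be HAM-A and none RAID.

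**What is untouched.** Section 2.4 bases the sample size on QoL-AD: 16 subjects, and 16 / (1 − 0.20) = 20 after dropout, as stated. The 16 is also reproduced for a within-between interaction with the stated 35% read as f = 0.35, two groups, three assessments and an assumed correlation of 0.5 between assessments (power 0.837; the protocol gives no correlation). No anxiety scale enters this calculation.

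**The case against.** The strongest reply is that the article shows two conflicting labels and nothing about conduct. Section 2.6.1 refers to a separate data collection sheet, and section 2.2 to a second protocol version dated 20 April 2022. Neither is shown, and either could settle the matter. Nor is Table 2 perfectly exhaustive: the operator's observation, listed in Table 1, has no row there, although section 2.6.1 provides a checklist for it. Either scale name could be a drafting leftover.

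This stands, and it limits the point. A reader might infer that RAID will never be collected, or that the anxiety outcome is lost in full. The documents do not support either. Which scale is given is unknown. If Table 2 is followed, anxiety is still measured three times by HAM-A, and the NPI, given at the same visits, includes anxiety among its 12 symptoms (section 2.7.7), although it is declared for behavioural symptoms.

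A reader might also infer that the protocol itself rejects HAM-A, because section 2.7.3 says "it has been criticized for its sometimes poor ability to distinguish anxiolytic effects from antidepressant effects". That would be selective. The criticism is qualified by the word sometimes, and although the section notes that HAM-A has no standard set of questions, it goes on to call the scale's reported reliability acceptable. The merits of the two scales are not needed to show the inconsistency and do not decide which name is correct.

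What the reply does not do is remove the contradiction. This is not detail left to a fuller document: the article positively names two instruments for one outcome. A table row and a whole referenced subsection are also too much to be a text-extraction fault.

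**Conclusion.** The contradiction holds and should be corrected. Read literally, the declared anxiety instrument has no planned assessment and the scheduled one serves no declared outcome, which leaves the scale open to choice after the data are seen.

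The reach is one secondary outcome in a 20-patient pilot. QoL-AD as primary outcome and the sample size are unaffected. The figure of 0 of 3 RAID assessments depends on Table 2 being followed as written; that is an assumption, not a fact about the trial's conduct.

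A reader might also conclude that Table 2 is simply wrong and RAID should be written into it. The documents do not establish that. The abstract describes recruitment in the present tense, section 2.9 speaks of video analysis as already done, and the ethics statement says consent was given, so the trial may be under way. If HAM-A is the scale in use, writing RAID into Table 2 would make the schedule false.

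**What to change.** 1. Check which scale is on the data collection sheet and which has been given at T0.
2. Name that one scale in the abstract, section 2.1, Table 1 with its footnote, Table 2 and section 2.7.3.
3. If no baseline has been collected, keep the declared outcome: schedule RAID at T0, T1 and T2, and describe RAID in section 2.7.3.
4. If HAM-A has already been collected, declare HAM-A as the anxiety outcome in a dated amendment made before any unblinded look at the data. Notify the Ethics Committee, as section 4.1 requires for protocol modifications.
5. If the check shows that both scales are given, list both in Table 2 and state which one is the outcome.

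The cost is text corrections in five places, a form check and, where the protocol changes, the Ethics Committee notice. No extra visits are needed.

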#### Mini-mental state examination

2.7.1.

The instrument provides a score indicative of the degree and presence of any global impairment of cognitive function. Proposed for screening procedures. The score ranges from 0 to 30, scores ≥24 indicate normality, mild cognitive impairment between 18 and 23, between 11 and 17 medium cognitive impairment; ≤10 severe cognitive impairments. The reported score is adjusted for age and schooling (28).

#### Addenbrooke cognitive examination revised

2.7.2.

The ACE-R is a scale used in dementia. It consists of five different cognitive domains, for which separate scores can be calculated: attention/orientation (18 points), memory (26 points), verbal fluency (14 points), language (26 points) and visuospatial skills (26 points). The sum of the scores of the individual domains is equal to l00 which is the maximum score of the test. The administration takes an average of 15 min (29, 30).

#### Hamilton anxiety rating scale

2.7.3.

The HAM-A was one of the first rating scales developed to measure the severity of anxiety symptoms, and today it is still widely used in both clinical and research settings. The scale consists of 14 items, each defined by a set of symptoms, measures of both psychic anxiety (mental agitation and psychological distress) and somatic anxiety (anxiety-related physical complaints). Although the HAM-A remains widely used as an outcome measure in clinical trials, it has been criticized for its sometimes poor ability to distinguish anxiolytic effects from antidepressant effects and somatic anxiety effects from secondary somatic effects. The HAM-A does not provide any set of standardized questions. Despite this, the reported levels of reliability of the scale appear to be acceptable. Each item is scored on a scale from 0 (not present) to 4 (severe), with a total score range of 0–56, where <17 indicates mild, 18–24 mild to moderate, and 25–30 moderate to severe (31).

#### Cornell scale for depression in dementia

2.7.4.

This is a scale specially designed for the assessment of depressive symptoms in patients with dementia. The Cornell Scale uses a standardized set of items that are collected through an interview with a person who knows the patient (family member or caregiver) and semi-structured interview with the patient. It is therefore an observational instrument, which therefore does not require direct patient response to standardized formulated questions. The scale consists of 19 items, with responses that are graded from 0 (symptom absent) to 2 (symptom severe). It is one of the few scales validated in populations of subjects with dementia, including moderate–severe (32).

#### Quebec user evaluation of satisfaction

2.7.5.

The scale measures a person’s satisfaction with the device used. It consists of eight questions related to satisfaction with respect to the device in use and four questions with respect to the services associated with its provision. The user answers each question with a score ranging from 1 (completely dissatisfied) to 5 (very satisfied) (33).

#### Quality of life—Alzheimer’s disease

2.7.6.

The scale assesses the quality of life in patients with Alzheimer’s disease. It consists of 13 items (physical health, energy, mood, living situation, memory, family, marriage, friends, self as a whole, ability to do chores, ability to do things for fun, money, and life as a whole) to which the user gives a score between 1 and 4 (poor, fair, good, or excellent) (34).

#### Neuropsychiatric inventory

2.7.7.

The scale was developed to assess the neuropsychiatric symptoms and psychopathology of patients with Alzheimer’s disease. The 12 symptoms examined are: hallucinations, delusions, agitation, depression/ dysphoria, anxiety, euphoria/exaltation, apathy/indifference, disinhibition, psychoemotional irritability/lability, aberrant or aphinal motor activity, sleep disturbances, and appetite and eating disorders. Three aspects are investigated for each neuropsychiatric symptom: frequency (1, rarely, to 4, very frequently); severity (1, mild, to 3, marked); caregiver emotional and psychological distress (1, none, to 5, severe) (35).

#### Technology acceptance model

2.7.8.

The purpose of the TAM is to determine what factors influence the acceptance of a given technology, namely perceived usefulness and perceived ease of use, which also influences perceived usefulness. These factors determine attitude toward use, which in turn influences behavioral intention to use, which can be interpreted as acceptance of the technology. The questionnaire consists of 9 items, with responses on a Likert scale from 1 (“strongly agree”) to 5 (“strongly disagree”) (36).

### Data management

2.8.

All personally identifiable information gathered during the study will be managed and stored in compliance with the General Data Protection Regulation (GDPR) of 2018. The principal investigator will have control over the use of the study data. All records and documentation linked to the trial will be kept in accordance with relevant regulatory stipulations, and access to data will be restricted to authorized trial personnel.

### Data analysis

2.9.

A Plan of Analyses will be defined on the basis of which the analyses themselves will then be conducted. The first step of the analysis will be exploratory in nature. Descriptive analysis of the sample will be conducted using classical uni and bivariate statistical analysis techniques. Significant differences between outcomes and exposures will be compared using the Chi Square test, the Fisher Exact (in the case of categorical variables) or the *T*-test or the Anova test (in the case of comparisons of continuous variables between groups depending on whether or not they are normally distributed). In a second step, follow-up data analysis will be conducted in order to evaluate the effectiveness of the intervention. This phase of analysis will involve the use of the confounder assessment, that involves identifying and measuring potential confounding variables to ensure accurate estimation of causal effects, will be used. Techniques such as matching, stratification, or statistical adjustment through regression models will be used to account for confounding and obtain unbiased causal estimates. To assess the intervention’s effectiveness, techniques such as *t*-tests, chi-square tests, or analysis of variance (ANOVA) for continuous, categorical, or count outcomes, respectively will be used. These models compare the outcomes between the intervention and control groups, providing insights into the intervention’s impact. For the behavioral analysis, videos acquired during the interaction with Paro have been analyzed by the FaceReader software investigating facial expressions and generating a detailed report on the detected emotions, such as happiness, sadness, anger and fear. The information obtained from this analysis will be used to determine which emotion is most present during the interaction with Paro. Moreover, in the case of a semi-structured interview, data will be analyzed manually with the identification of themes, patterns, and commonalities across responses to provide insight into the research question.

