### Sample size

2.4.

QoL-AD (20) was used to perform a sample size calculation. Assuming an effect size of 35%, the total sample size needed to capture this effect size was estimated to be 16 subjects, assuming a statistical power of 80%, a significance level of 0.05, two groups and 3 repeated assessments (one baseline, 2 follow-ups) in a within-between interactions ANOVA model. Even assuming a drop-out rate of 20%, the total required sample size would be 20 subjects (10 in each arm).

This sample size is assumed to be more than sufficient to capture variation even for secondary outcomes for which treatment effect sizes are assumed to be similar or larger than those identified for the primary outcome.

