### Recruitment

2.5.

Patients are selected by the Alzheimer’s Day Center team of the Neurology Operating Unit, IRCCS INRCA, in the Ancona branch. These patients will be contacted by the center manager to schedule an interview with family members. Once they have verified that they meet the inclusion and exclusion criteria of the study and acquired the informed consent in duplicate, signed by both the patient and the family member, the center’s qualified staff will proceed to the baseline assessment with the questionnaires and clinical tests stipulated in the study design. A randomization technique based on a single sequence of random assignments is used. A list of random numbers generated by the computer is used and subject is assigned a number based on their order of inclusion in the study. According to this technique, the subjects are randomly assigned to one of the two study groups. At the end of intervention and after an additional 3 months, the above patients will be evaluated again.

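### Section 2.9 prescribes observational confounding control, with matching among the options, as the route to an unbiased effect in a randomised trial of 20 patients

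*Protocol article*

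**What the plan says.** The Recruitment section (2.5) describes a computer-generated list by which "the subjects are randomly assigned to one of the two study groups". It names no stratification factors.

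The Sample size section (2.4) says that "the total sample size needed to capture this effect size was estimated to be 16 subjects". The inputs are 80% power, a 5% level, two arms and three measurement times, and the test is the group-by-time interaction "in a within-between interactions ANOVA model". Attrition is then allowed for, which brings the total to 20, with 10 per arm. The section mentions neither matching nor covariates.

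The Data analysis section (2.9) has an exploratory step and then an effectiveness step. Of the effectiveness step it says: "This phase of analysis will involve the use of the confounder assessment". It continues: "Techniques such as matching, stratification, or statistical adjustment through regression models will be used to account for confounding and obtain unbiased causal estimates". No covariate is named, no selection rule is given, and no choice is made among the three techniques. The section then lists t-tests, chi-square tests and ANOVA for the effect of the intervention, and it announces that a separate plan of analyses will be defined.

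**The concern.** Matching, stratification and regression to remove confounding are the tools of a cohort study, where patients in the two groups differ systematically. Here allocation is by chance. Baseline differences between arms are therefore random, and their effect is already covered by the standard error of the comparison. In a randomised trial, adjustment serves to gain precision and does not create unbiasedness.

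Two things are at stake. With 10 patients per arm, one of the permitted techniques (matching) can shrink the sample well below what the sample-size section calls for. And if technique and covariates stay open until outcomes are known, the result can depend on the choice. A later plan of analyses that followed section 2.9 faithfully would carry the unsuitable rationale forward.

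**Working it through.** **1. The plan's own figure.** Inputs from section 2.4: effect size 35%, two groups (k = 2), three assessments (m = 3), alpha 0.05, power 80%, drop-out 20%. Assumptions, because the article does not state them: the effect size is Cohen's f = 0.35, the correlation between assessments is rho = 0.5, and sphericity holds.

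For the group-by-time interaction: lambda = f² × N × m / (1 − rho), df1 = (k − 1)(m − 1), df2 = (N − k)(m − 1).

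At N = 16: lambda = 0.1225 × 16 × 3 / 0.5 = 11.76, df1 = 2, df2 = 28, power 0.837. At N = 14 power is 0.774, so 16 is the smallest total with equal arms that reaches 80%. Drop-out: 16 / 0.8 = 20. The stated figures are reproduced. The result is sensitive to rho: at N = 16, power is 0.53, 0.69, 0.84 and 0.97 for rho = 0, 0.3, 0.5 and 0.7.

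**2. Is confounding control needed for an unbiased effect?** Null trials were simulated with 1:1 randomisation, five candidate baseline covariates, one of which explains R² = 0 or 0.3 of the outcome variance, and 6,000 replicates per setting. The mean unadjusted estimate lay within 0.01 outcome SD of zero in all four settings (n = 16 or 20), which is simulation noise.

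One covariate fixed in advance also gave an estimate centred on zero. With R² = 0.3 and n = 20 it cut the SD of the estimate from 0.445 to 0.377 (0.377 / 0.445 = 0.85). With R² = 0 it cost a little (0.449 to 0.463).

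**3. What would matching cost?** Assumption: 1:1 greedy matching within 0.2 SD, on the covariate itself or, for several covariates, on a linear score; 4,000 replicates. The article mentions no caliper.

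| Covariates | Pairs kept of 10 (n = 20) | Patients | Pairs kept of 8 (n = 16) | Patients |
|---|---|---|---|---|
| 1 | 5.1 | 10 | 3.7 | 7 |
| 3 | 4.7 | 9 | 3.2 | 6 |
| 5 | 4.2 | 8 | 2.8 | 6 |

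Optimal matching instead of greedy gives much the same: 5.3 of 10 pairs on one covariate at 0.2 SD, and 4.2 pairs on two covariates at 0.5 SD.

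Putting the reduced totals into the formula of step 1:

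- N = 10: lambda = 0.1225 × 10 × 3 / 0.5 = 7.35, df2 = 16, power 0.59.
- N = 8: lambda = 5.88, df2 = 12, power 0.47.
- N = 6: lambda = 4.41, df2 = 8, power 0.33.

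These are indicative only, since the formula gives no credit for any gain from pairing.

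Without a caliper, 10 patients can be paired with 10 and nobody is lost, but some pairs will be poor matches. Stratification and regression exclude nobody in themselves.

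**4. What would open covariate choice do to type I error?** These are the null trials of step 2, with nominal level 5% and a simulation standard error near 0.3 percentage points (√(0.05 × 0.95 / 6000) = 0.0028).

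| Rule | Rejection rate over the four settings |
|---|---|
| Unadjusted | 4.6-5.2% |
| One covariate fixed in advance | 4.3-5.3% |
| Covariates imbalanced at p < 0.2 | 3.5-4.8% |
| Covariates associated with outcome at p < 0.2 | 4.5-5.1% |
| Change in estimate above 10% | 5.0-7.0% |
| Best p-value over sets of up to two covariates | 11.1-15.0% |

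A separate simulation with baseline QoL-AD, six other covariates and the smallest p-value over eight models gave 12.3%. Only selection by the result itself inflates the error materially.

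**The case against.** The strongest reply is that this is a condensed article, that it announces a separate plan of analyses, and that naming covariates and choosing among techniques is ordinary content for that plan. This stands as far as missing detail goes: the absence of a covariate list is not the point here. It does not rescue the rationale, which the article states outright and which does not fit a randomised comparison, nor the inclusion of matching.

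Several stronger readings are tempting, and the text does not support them:

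- **A data-driven search.** A reader might infer that confounders are picked from the trial results, because an exploratory step precedes the effectiveness step. The article says that confounders will be identified. It does not say how or when, and it does not tie the exploratory tests to covariate choice.
- **Patients will be discarded.** The three techniques are alternatives, and regression is one of them. Loss of patients needs matching with a caliper, which the article does not mention.
- **The 5% level is lost.** The rates of 11-15% belong to selection by best p-value, a rule the article never states.
- **Baseline significance testing.** The exploratory tests compare outcomes and exposures. Whether that means baseline comparisons between arms is unclear, so no criticism is built on it.

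It can also be said that randomisation does not protect against differential drop-out, and that 20% drop-out is expected. That is true. But the article does not give it as the reason for confounding control, and matching the patients who remain would not be the natural answer to it.

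**Conclusion.** The point holds in a limited form. Section 2.9 states an observational rationale for a comparison that randomisation already makes unbiased in expectation, bias from differential drop-out aside. Of the three techniques offered, matching is unsuitable at this size, because the choice lies between a caliper that roughly halves the sample and loose balance. Regression on covariates fixed in advance is valid, keeps everyone and can gain precision, so the section already contains the better option without committing to it. Inflated type I error is a possibility that the open wording leaves, not a consequence of the plan as written.

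The figures rest on assumptions absent from the article: the metric of the effect size, rho, the caliper, the number of candidate covariates and their R². The argument that confounding control is not needed for unbiasedness depends on none of them. This should be changed, but it does not by itself undermine the trial.

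**What to change.** In section 2.9:

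- Remove matching, and the statement that confounding control is what makes the effect estimate unbiased, from the effectiveness analysis.
- State one primary comparison of all randomised patients by assigned arm, using a regression model (ANCOVA or repeated measures) adjusted for baseline QoL-AD and at most also for MMSE at recruitment. Fix it before the data are seen. Table 2 already schedules both measures, so no new data are needed.
- Label any other adjustment, and any stratified analysis, as sensitivity analysis.

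The cost goes slightly beyond wording. The article names no single primary model, so one must be chosen and aligned with the ANOVA of section 2.4. That calculation counts the baseline as one of three repeated assessments. If baseline QoL-AD becomes a covariate, it should not also be an ordinary response in the same model, and the sample-size statement should say how the two correspond.
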